# Background – Review of evidence-based treatment for chronic midportion Achilles tendinopathy

Achilles tendinopathy (AT) is a common condition, particularly in those who run. It is a chronic, activity-limiting syndrome, defined by the presence of pain and thickening in the Achilles tendon.^1^ The lifetime prevalence of AT is 52% in former runners, and the annual incidence is 7%– 9% in current runners.^2^ Onset is typically chronic in nature, although occasionally a patient may present with an acute tendinopathy. There has been a largely successful (although controversial) movement to abandon use of the term “tendinitis” for patients with symptoms that last longer than three months, in recognition of the need to address degenerative structural changes within the tendon (i.e. angiofibroblastic tendinosis) rather than inflammation, which is argued to be rarely or only minimally present in most cases.^3^

The high prevalence among runners points to mechanical loading as an important etiologic factor.^4^ In vitro and in vivo research from the laboratory of [name] and others suggests that periods of mechanical overuse result in subclinical evidence of inflammatory or pseudoinflammatory change.^5-16^ The term “pseudo” is used here to recognize that although cellular inflammation may not be present in an overloaded tendon, we have discovered that tenocytes themselves produce certain inflammatory mediators in response to increased mechanical loading, such as substance P, prostaglandin E2, VEGF, glutamate, and others. Over time, repeated episodes of inflammatory activity have been shown to lead to cumulative changes in the tendon, eventually resulting in the development of tendinosis, paratendonitis or both.^5 17^

A minority of patients with AT have sedentary lifestyles and no identifiable history of mechanical overload, which demonstrates that while external mechanical loading is a risk factor, individual biomechanical^18 19^ and systemic^2^ influences are also likely to be important (as is the case in primary OA). Indeed, multiple risk factors have been identified in small associational studies, including advancing age,^2^ male sex,^2^ high body mass index,^20^ hypercholesterolemia^21^ and the presence of genetic variants of genes related to collagen metabolism.^22 23^

In this introductory section, we review the evidence base for conservative management of chronic midportion AT. Any new treatment must be evaluated in the context of the current evidence base and be tested on a background of the current standard of care.^24^ A plethora of conservative treatments have been suggested to provide relief from, or “cures” for, AT, including nonsteroidal anti-inflammatory drugs (NSAIDs), ultrasound and laser therapies, nutritional supplements, friction massage, and various injection strategies. For the details on the systematic search strategy used for this section, please see the published version of this review in CMAJ, Appendices.^25^

**Is exercise an effective treatment?**

The strongest evidence (multiple, consistent, well controlled trials) supports heavy-load exercise as the cornerstone of managing AT. This form of exercise varies slightly from trial to trial, but the principal goal is to provide a strong, controlled, mechanical force to the Achilles tendon which is tolerable to the patient. This is usually achieved through eccentric (lengthening) muscle activity; for instance, a heel drop over a step. (In contrast, concentric exercise involves a toe raise that would contract the calf muscles.) As the patient’s tolerance of the exercise improves, the load is progressively increased (e.g., by progressing from bilateral to unilateral heel drops, by progressing the degree of dorsiflexion, by adding weights in a backpack or through use of gym equipment). Rompe and colleagues found this type of progressive, slow, heavy-load exercise to be superior to a wait-and-see strategy, with a 60% success rate in the exercise group (95% confidence interval [CI] 41%–79%) compared with 24% in controls who did not receive treatment (95% CI 7%–41%).^26^ Eccentric exercise was found to be superior to a standard exercise program in a multicentre randomized trial by Mafi and colleagues; 82% of the patients who trained with eccentric exercise were satisfied and had returned to their previous activity level after 12 weeks (95% CI 66%–98%), compared with 36% of patients who trained with standard (concentric) exercise (95% CI 16%–56%).^27^ Thus, eccentric exercise induces clinically meaningful effects but may take several weeks or months before a benefit is felt, and not every patient is guaranteed to respond. The potential harms of eccentric exercise include delayed-onset muscle soreness or exacerbation of the tendinopathy (e.g. pain, soreness or swelling). These typically occur when the exercises are performed too quickly, with incorrect biomechanics, or with an increase in load that is too abrupt. There are no published reports of tendon rupture in response to eccentric loading.

**Do orthotics, braces or splints have a positive effect?**

Orthotics may be helpful in conjunction with other modalities of treatment if there is an identifiable malalignment, whereas braces or splints do not appear to improve outcomes in Achilles tendinopathy. One randomized controlled trial of male runners found a significant improvement in pain in patients wearing custom-made orthotics. Of the patients, 89% described a reduction in pain scores of greater than 50% after four weeks of wearing custom insoles (95% CI 69%–100%), compared with 0% in control patients who did not receive treatment (*p* < 0.05).^28^ This trial may have been improperly blinded, because sham insoles were not provided to the control group. Referral to a qualified orthotist should be considered if the biomechanical examination identifies a potentially correctable malalignment. However, there is little evidence to suggest that orthotics alone will be effective in most cases. An inflatable brace was examined in two separate studies. The brace is commercially available (AirHeel [Aircast]) and designed to be worn during activity. An earlier study by Petersen and coworkers could not detect differences between groups and recommended further study.^29^ In a subsequent larger study, Knobloch and colleagues randomly assigned 116 patients to undergo treatment consisting of eccentric training or eccentric training plus prescription of an AirHeel brace. Both groups achieved similar improvements in pain after 12 weeks, which showed that the addition of the AirHeel brace did not improve the success of rehabilitation.^30^ Other authors have advocated use of a night splint, as commonly prescribed for patients with plantar fasciitis. de Vos and colleagues randomly assigned patients to complete a heavy load eccentric training program with or without use of a night splint. After 12 weeks, 63% of patients in the group that received only exercise were satisfied (95% CI 47%–79%), compared with 48% in the night splint group (95% CI 32%–64%), and there were no significant differences in pain or other outcome measures.^31^

**What is the role of physiotherapy**?

Many clinicians recognize that an individualized physiotherapy program that addresses the patient’s specific presentation, loading history and biomechanics, leads to the most effective outcomes when combined with exercise. However, published evidence for these complex interventions is lacking, particularly for longer-term outcomes. One trial examined the short-term effect of physiotherapy, including ice, transverse friction massage, therapeutic ultrasound and exercise (i.e., concentric, eccentric, balance and proprioceptive drills), compared with control (no treatment).^28^ The physiotherapy group (*n* = 11) experienced significant improvements in activity-related pain compared with controls (*n* = 8) (*p* < 0.05). Effect size could not be calculated from the reported data, which made a comparison with other trials that used exercise alone impossible. The trial included only men and used a multimodal intervention that closely approximates interventions currently provided by many sports medicine physiotherapy clinics. Although this improves generalizability, it makes it impossible to distinguish the effective components of the program.

**Nonsteroidal anti-inflammatory drugs**

This review did not identify a randomized controlled trial of NSAIDs that met the inclusion criteria of symptoms lasting longer than three months. One trial of NSAIDs included some patients with chronic Achilles tendinopathy of less than six months’ duration; that trial was rejected for inclusion during the initial literature search (Appendix 1, available at www.cmaj.ca) because it also included patients with acute Achilles tendinopathy. This trial found identical treatment outcomes in 70 patients randomly assigned to receive piroxicam or placebo tablets.^32^ The study is consistent with a lack of effect of NSAIDs in other types of tendinopathy, e.g. tennis elbow.^33^

**Injection therapies**

Several injection therapies for the treatment of chronic Achilles tendinopathy have been examined in small clinical studies. These treatments include corticosteroids, sclerosing therapy, aprotinin, polidocanol, glycosaminoglycan polysulfate, prolotherapy, and platelet-rich plasma.^34-40^ Several studies have reported trends that are consistent with a clinically significant improvement, but are hampered by the small number of patients studied. Fredberg and colleagues randomly assigned 24 patients with midportion Achilles tendinopathy to receive ultrasonography-guided corticosteroid (20 mg triamcinolone) or placebo injections. The authors commented that a significant number of patients treated with corticosteroid injection experienced initial improvements followed by a relapse of symptoms, but it is difficult to extract this information from the trial.^37^ An older study included instances of both acute and chronic Achilles tendinopathy: these authors reported a lack of success with corticosteroid injection for the subset of patients with chronic Achilles tendinopathy.^36^ One randomized controlled trial examined the effect of injection of platelet-rich plasma on patients with Achilles tendinopathy; however, the study included patients with relatively acute conditions (two months’ duration of symptoms) and thus did not meet our a priori inclusion criteria.^41^ Platelet-rich plasma is sometimes considered for instances of chronic, refractory tendinopathy, but there is as yet no evidence from randomized controlled trials to support or refute its use for chronic midportion Achilles tendinopathy^40^. A recent RCT of prolotherapy + eccentric loading exercise (PLE) vs eccentric loading exercise (ELE) reported accelerated recovery in the PLE group; the outcomes were encouraging (7/14 in PLE group achieved an improvement of 20/100 in Victorian Institute of Sports Assessment–Achilles [VISA-A-A] score compared to only 3/15 in the ELE group at 6 weeks)^42^ however this treatment has not yet become part of the first line standard of care.

**Extracorporeal shock wave therapy**

As for injection therapies, the current evidence for shock wave therapy as a treatment for Achilles tendinopathy is promising but inconclusive. Shock wave therapy involves the application of acoustic waves that vary in nature according to the type of device used and the amount of energy and energy flux delivered to the tissue. The evidence that met our criteria rested on two trials from the same group.^26 43^ One trial examined the effect of adding low energy (0.1 mJ/mm^2^) extracorporeal shock wave to a heavy-load eccentric exercise program. Patients who were randomly assigned to receive active shock waves plus exercise fared slightly better in terms of pain (1.5/10 improvement on a visual analogue scale; *p* = 0.0045), activity level (13.5/100 improvement on the VISA-A-A score; *p* = 0.016) and satisfaction with treatment at four months.^18^ Although statistically significant, these average values are rather small; the minimum clinically significant difference for the VISA-A-A score is 15/100, and for pain it is 2/10. However, only mean values were presented – the actual percentage of patients who achieved a clinically significant improvement in each group was not reported.

**Glyceryl trinitrate**

Two randomized controlled trials examined the effect of placing patches of glyceryl trinitrate directly over the painful Achilles midportion. Nitric oxide is essential to achieve normal healing of the tendon after acute injury; therefore, it may also be helpful in promoting repair of chronic injuries.^44^ Paoloni and colleagues randomly assigned 65 patients to receive rehabilitation (focusing on active tendon-loading exercises) plus glyceryl trinitrate for six months, or identical rehabilitation with placebo patches.^45^ The primary outcome measure was patient-rated tendon pain with activity. Four patients did not conclude the trial because of the development of headaches or skin rashes. In those who remained in the trial, there was a statistically and clinically significant decrease in pain with activity (*p* = 0.03). A second study by Kane and coauthors examined the effects of patches of glyceryl trinitrate and eccentric exercise versus placebo patches and eccentric exercise in 40 patients (20 per group).^46^ The main outcome measures were the Ankle Osteoarthritis Scale pain and disability scores. The scores of both groups were significantly decreased at six months, but the average scores were identical in the two groups. Thus, the initial promising results from Paoloni and colleagues’ trial have not been supported by similar studies in other centres.

**What is the prognosis?**

Although tendinopathy may seem a relatively benign soft tissue pathology, recovery often follows a prolonged time course, even with ideal treatment. Because traditional surgical management has only a 50% rate of success,^47^ it is essential to ensure that the best conservative management has been offered before consideration of surgery. The recalcitrant nature of chronic Achilles tendinopathy was documented by Rompe and colleagues, who noted that there was a slow but gradual improvement in the average load-induced pain score from 7.9/10 to 5.9/10 over the course of four months in patients not receiving treatment. After this period, only 24% of these patients reported themselves as much improved or cured.^26^ In the long term, the prognosis of chronic Achilles tendinopathy is more favourable. At eight-year follow-up in one study of 83 patients, 80% of patients were back to full physical activities, whereas 20% reported that their physical activity was still impaired as a result of the Achilles tendinopathy.^48^

# Intramuscular stimulation – rationale for its use in chronic Achilles tendinopathy

Currently, there are no clinical or laboratory studies on the effect of IMS on Achilles tendinopathy. However, [name] has convincingly presented the rationale for IMS therapy for this condition.^49^ IMS practitioners have noted that chronic pain conditions like tendinopathy are almost always accompanied by areas of chronic muscle tension and shortening that may create increased strain in associated tendons.^49^ Recent work has established that strain, rather than load per se, is the primary driver of tendon microdamage during cyclic loading.^50^ Additionally, focal areas of muscle thickening could create nonhomogenous strains and/or shearing within the Achilles tendon.^51^ During a typical running gait cycle (males running at 12 km/hr), the Achilles tendon is subjected to strains in the range of 3.8 ± 2%^52^, meaning that the tendon is functioning in the linear area of the load-displacement curve, just under the yield point where more substantial fatigue damage begins to accumulate (~5%)^50 53^. Muscle shortening as a whole, or localized areas of shortening within the whole muscle, would lead to slight but potentially significant increases in the strain experienced by and within the tendon, whereby the tendon could experience injuriously higher peak strains (i.e. above 5%). If IMS can alleviate localized foci of muscle shortening as noted clinically, then the strain levels within the tendon may be lessened. This would tend to minimize ongoing fatigue damage experienced by the tendon (for instance, when a patient engages in running or jumping activities).

Sustained whole muscle stretching is frequently used by therapists when treating tendinopathies^.(e.g 54)^ However, localized areas of shortened muscle (i.e. the tender/painful bands or “trigger points” targeted by IMS) clinically do not respond well to this type of stretching. Muscle shortening in the gastrocnemius and soleus muscles is clinically observed as a reduction in dorsiflexion range of motion (ROM) with the knee straight or bent. Achilles tendinopathy has been associated (in cross-sectional case control studies) with a reduced range of dorsiflexion ROM.^19^ Indeed, dorsiflexion ROM has been used as a secondary outcome measure in clinical trials of Achilles tendinopathy.^55^ IMS may effectively and efficiently restore normal DF ROM by releasing tight muscle bands.

IMS may also have a role to play in restoring a neurotrophic effect to tendon tissue to normalise collagen turnover and tendon strength.^49^ Additionally, direct needling of tendon (a technique included in the IMS armament of needling procedures) can stimulate a local inflammatory response and the release of growth factors such as platelet-derived growth factor.^56^ IMS may therefore have a role to play in stimulating healing in tendinosis.

# Study Design

This is a prospective, single blind, randomized controlled trial with three groups. All groups will receive standard 12 week physiotherapy program provided by LS, including a standardized and progressive eccentric training and strengthening program. The first group will receive IMS (detailed below), while the second will receive an equivalent number of sham (superficial non-intramuscular) needling sessions. The third receives the progressive exercise training program alone. Patients will be recruited from the clinical practice of LS and colleagues; additionally, the study will be advertised through LS’s and AS’s contacts in the IMS, UBC, Physiotherapy Association of BC, and Vancouver Coastal Health networks. After providing informed consent and being screened for inclusion/exclusion criteria, diagnosis will be confirmed by physical examination. Inclusion criteria include subjects 19 to 60 years of age, fluent in English, with a 3 month minimum symptom duration, evidence of midportion Achilles tendinopathy on physical examination and tendinosis on ultrasound; and objective signs by Gunn IMS assessment of neuropathic change in the L5-S2 segmental levels including the presence of taut muscle bands amenable to IMS.^49^ Tight bands palpated in muscles paraspinally (dorsal rami) from T1 down and peripherally (ventral rami) from T12 down will also be treated in the IMS group, but participants without findings in the L5-S2 levels will be excluded to limit variability among subjects. Exclusion criteria include IMS contraindications (infection in the area, pregnancy, bleeding disorders, history of bacterial endocarditis, post-surgical implant in last four to six months and major surgery in the last three months), previous treatment with IMS or TCMA (for blinding purposes); true leg length difference of greater than ½” previous corticosteroid injections or recent fluoroquinolone use and systemic inflammatory disease. Those demonstrating the presence of other syndromes that cause pain in and around the Achilles tendon will be excluded by history-taking and physical examination: partial tearing, posterior ankle impingement/ os trigonum syndrome, tenosynovitis, dislocation of the peroneal or other plantar flexor tendons, irritation or neuroma of the sural nerve or insertional Achilles pain. Patients will be randomized by the research assistant ([name]) who is blinded to the patient’s baseline data using a random number generator (SPSS v.16.0).

## Study Team and Roles

**[name]**

Conduct initial phone screen (with [name] and [name]).

After final eligibility screen by [name] and informed consent obtained, consult random number generation table and record subject group allocation, ensure confidentiality of files (must be in a locked cabinet accessible only by the study team).

Collate initial subject files and deliver to locked cabinet at Kinetic clinic.

Prepare patient exercise diary with appropriate dates filled in.

Collect hard copies of data (VISA-A forms and Global Improvement forms completed by study participants, ankle ROM forms completed by MB, treatment attendance data logged by LS) from locked cabinet at Kinetic and enter into Master Tracking Sheet on password-protected computer.

Monitor patient flow through study, ensure all appointments are booked and confirmed when they happen, including assessment by MB and UTC scans by LS, as per Master Tracking Sheet.

Maintain unblinding log.

Contact participants re 1 year follow-ups.

Send de-identified data (e.g. copies of Master Tracking Sheet) to [name] or designate upon request.

**[name]**

Oversee recruitment strategy, distribution of posters and study materials. Conduct initial phone screen (with [name] and [name]).

Conduct physical assessment screen.

Obtain informed consent. (Documents to be stored in locked cabinet at Kinetic for collection by HD).

Create tracking sheet for ankle range measures, VISA-A questionnaires (n= 4 x 42 = 168), Global Improvement scales (n= 4 x 42 = 168), and unblinding sheets for [name] and deliver to locked cabinet at Kinetic.

Collect ultrasound tissue characterization (UTC) images.

Interpret UTC images (with [name]).

Provide dry needling and exercise treatments and progressions.

Report unexpected events (per UBC Nov 11 2012 policy) to [name].

Track study expenditures.

Remain blinded to VISA-A / Global Improvement scores / ROM scores.

Record patient attendance dates and store in locked cabinet for [name] to access and record on Master Tracking Sheet.

Ensure data stored securely.

Deliver data from Canopy to Kinetic for collection by HD.

Primary contact in case of adverse event.

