**IMS treatment group**

Intramuscular Stimulation (IMS) involves the insertion of fine sterile needles into tender and painful points in tight muscle bands (hypothesized in the IMS literature to be caused by reduced nerve supply).^49^ Needles inserted into muscles create an electrical discharge.^49^ In patients with chronic musculoskeletal pain syndromes, this discharge is strongly exaggerated and results in twitches, fasciculations or sustained contractions in the targeted muscle.^49^ Patients will feel these various muscular reactions, with the sustained contractions producing a distinctive deep aching sensation that is cramp-like in quality.^49^ This sensation is analogous to the Teh Ch’i or Deqi Phenomenon in Traditional Chinese Medicine Acupuncture (TCMA) literature.^49^ Treatment will be guided by the findings of the assessment, which will have paid particular attention to signs in groupings of muscles supplied by both the dorsal and ventral rami of the same segmental spinal level. Muscles in the periphery that have demonstrated tight bands or reduced muscle lengths will be treated with IMS by one of the investigators (LS). Muscles at levels of the spine that have demonstrated tight muscle bands, signs of trophedema or tender, prominent spinous processes will also be treated. Those muscles that respond to needle penetration with sustained contractions or “needle grasp”, such that resistance is felt on attempting to withdraw the needle, will be left in situ until the muscle releases. This may occur quickly, but may be expected to take up to twenty minutes.^49^ Those muscles that respond with only fasciculations or twitches may be treated with extra stimulation by “fanning” or “twirling”, depending on patient tolerance, but needles will then be promptly removed. Needles will also be briefly inserted into the Achilles tendon to produce a local inflammation-healing response.^49^ The IMS group will receive treatment once a week for the first six weeks of the trial and once every two weeks for the remainder, resulting in nine treatments overall.

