All subjects will be entered into the rehabilitation programme at Stage 1. Subjects will be progressed based on a twenty four hour response to exercise, specifically there must not be pain or stiffness the morning after undertaking the exercise. Pain during exercises will be allowed as long as it is not more than 5/10 pain on a zero to ten scale, where zero is no pain at all and ten is the worst possible imaginable pain. Through all four stages, those subjects in the IMS group and the sham needling group will be advised to rest from their ELE and exercise generally (including stretches) after their treatment for the remainder of the day and the entire next day. From Stage 2 on, this rest day will be scheduled to coincide with the day seven rest day that all groups will observe. They will be instructed to recommence their exercise program the morning after. This is standard advice given to patients receiving IMS treatment.

All subjects will be advised that they may participate in pain-provoking activity, such as running, as long as their pain does not reach greater than 2-3/10 (Visual Analogue Scale) during the activity and as long as pain has returned to baseline by the following morning. The provocation of this level of pain up to 5/10 VAS during rehabilitation has been shown to not hinder recovery.^48 66^

The exercise technique and progression will be reviewed every two weeks until 12 weeks (6 reviews total).

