**Outcome measures**

The primary outcome measure for which the study is powered is the 12 week VISA-A score - a well validated and reliable disease-specific outcome measure, which also includes an activity-related pain scale.^67^ Secondary outcome measures include treatment success/failure, and muscle length (dorsiflexion ROM). Patients will rate themselves from 0 (very much worse) to 6 (very much improved). Scores of very much improved or much improved will be categorized as successes.^68^ Dorsiflexion range of motion with knee bent and straight will also be measured using an inclinometer, giving an indication of the effect of IMS and exercise vs exercise alone on muscle extensibility. These measures will be taken at 0 and 12 weeks, as well as at 52 weeks.[[1](#_ENREF_1)] After 12 weeks and 6 months of intervention, UTC scanning will be conducted to determine, as a pilot study, whether there is any subjective indication of a potential effect of IMS on tissue remodeling that could be pursued with a mechanistic study in future.

Muscle length measures will be made according to the protocol described by Norkin and White^69^ and Kendall and colleagues^70^ by a physiotherapist (MB) unaware of the treatment allocation. The two-joint plantarflexors (gastrocnemius and plantaris) will be measured in supine with the knee extended. The one-joint plantarflexors will also be measured in supine but with the hip and knee flexed 90 degrees or more to make the two-joint plantar flexors slack across the knee joint. The ankle will be passively dorsiflexed and the angle achieved measured by goniometry. The fulcrum will be centred over the lateral aspect of the lateral malleolus, the proximal arm will be aligned with the lateral midline of the fibula, using the head of the fibula for reference, and the distal arm will be positioned parallel to the lateral aspect of the fifth metatarsal. The ankle will be dorsiflexed to end-of-range (firm muscular end-feel) by pushing upward across the plantar surface of the metatarsal heads, without allowing the foot to rotate into inversion or eversion. Intratester reliability in measuring passive ankle dorsiflexion by goniometry has been shown to have an Intraclass Correlation Coefficient (ICC) of 0.91 for more experienced therapists.^71^ MB has had over three decades of musculoskeletal clinical experience.

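### Only unexpected events are reported, by the unblinded therapist who gives the needling; expected and minor adverse events are not collected systematically by arm

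*Protocol*

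**What the plan says.** All references are to the protocol.

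- **Reporting duty.** Under Study Team and Roles, the treating therapist is to "Report unexpected events (per UBC Nov 11 2012 policy". The same list has this person "Provide dry needling and exercise treatments and progressions" and act as "Primary contact in case of adverse event". The investigator to whom events pass reviews unanticipated problems only.
- **Blinding.** Scientific rigor states that the treating therapist cannot be blinded.
- **Data collected.** The research assistant's list names VISA-A forms, global improvement forms, ankle range-of-motion forms and attendance. It names no adverse-event form.
- **Outcomes and analyses.** Outcome measures gives VISA-A at 12 weeks as primary and then says "Secondary outcome measures include treatment success/failure, and muscle length (dorsiflexion ROM". Statistical analysis adds later VISA-A time points, but no harm measure.
- **Foreseen harms of the exercise.** The background states: "The potential harms of eccentric exercise include delayed-onset muscle soreness or exacerbation of the tendinopathy (e.g. pain, soreness or swelling".
- **Needling.** IMS treatment group describes a cramp-like ache and says "Needles will also be briefly inserted into the Achilles tendon to produce a local inflammation-healing response".
- **Contact.** IMS is given weekly for six weeks, then fortnightly, nine treatments in all. Sham has an equivalent number (Study Design). For exercise, "The exercise technique and progression will be reviewed every two weeks until 12 weeks (6 reviews total".
- **Prior evidence.** "Currently, there are no clinical or laboratory studies on the effect of IMS on Achilles tendinopathy".

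**The concern.** A rule limited to unexpected events leaves out the events one would most expect when needling is added to tendon loading: soreness, a flare after a session, swelling, bruising. The exercise harms occur in every arm. The comparative question is whether needling adds to them, and no data stream is set up to answer it.

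Events that do come to light would be ascertained differently by arm, because the reporter knows the allocation and sees needled patients more often. A difference in counts could reflect that alone, and an absence of reports could be mistaken for safety. Since the protocol says IMS has not been studied in this condition, readers would look to this trial for its harms as well as its benefit.

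**Working it through.** **1. What each instrument can record**

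| Source | Expected or minor events by arm? |
|---|---|
| Therapist's reporting duty | No: unexpected events only |
| Investigator's review | No: unanticipated problems only |
| Therapist as adverse-event contact | Patients have someone to call, but no recording or forwarding duty is stated |
| VISA-A (includes an activity-related pain scale) | Partly: net state of the tendon at the form date |
| Global rating (0 to 6, lowest category is marked worsening) | Partly: net change, self-rated |
| Range-of-motion and attendance forms | No |
| Exercise diary | Content not described, and not on the list of data collected |

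One foreseen harm, lasting exacerbation, is thus compared between arms through VISA-A and the global rating. A flare that has settled by the form date is not. Nor is bruising, infection or pain from needling. An infection might count as unexpected and be reported, but no form would hold it.

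**2. Contacts at which an event can surface in 12 weeks**

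The plan gives the totals. The week numbers are my reading of the schedule.

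- IMS and sham: weeks 1 to 6, 8, 10 and 12, so 6 + 3 = 9.
- Exercise alone: weeks 2, 4, 6, 8, 10 and 12, so 12/2 = 6.
- If exercise reviews share needling visits, which the plan does not say: 9/6 = 1.5 overall, and 6 against 3 by week 6.
- If reviews were wholly separate visits: (9 + 6)/6 = 2.5.

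IMS and sham have equal contact. The imbalance affects only the comparisons with exercise alone.

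**3. Form dates**

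The blinded assessor's list gives entry, 6 weeks, 12 weeks and 1 year, which matches the stated 4 × 42 = 168 forms. Outcome measures lists 0, 12 and 52 weeks. Statistical analysis plans VISA-A change at 6 and 12 months. A 6-month form is therefore implied in one place and not provided for in the others.

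**4. What 14 per arm can show if events are collected**

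The plan gives no figure on harms. Its sample size does reproduce: the SD of change is √(2 × 15² × (1 − 0.80)) = 9.49, against 9.5 stated. With 33 evaluable patients and 20% dropout, 33/0.80 = 41.25, so 42. Equal allocation, which I assume, gives 14 per arm enrolled and 11 evaluable.

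The exact one-sided 95% upper limit with zero events is 1 − 0.05^(1/n):

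- n = 14: 19.3%
- n = 11: 23.8%

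The power of a two-sided Fisher test between two arms, at event rates assumed only for illustration:

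| Rates | 14 per arm | 11 per arm |
|---|---|---|
| 50% v 10% | 54% | 36% |
| 50% v 20% | 26% | 17% |
| 30% v 10% | 14% | 8% |

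These limits come from the trial's size and would remain after the fix. They support descriptive counts rather than a formal test, and they show why an absence of reports cannot be read as safety.

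**The case against.** The strongest reply is that worsening is already measured. VISA-A contains a pain scale, the global rating runs down to marked worsening, patients complete both, and a blinded assessor hands them out. That stands. A reader might infer that the harms the protocol foresees are never compared between arms, and the text does not support this: net exacerbation is compared. What remains outside is anything transient or unrelated to tendon function.

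Three other strong readings also fail.

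- *The cramp-like ache and tendon inflammation are harms that the authors foresee and ignore.* IMS treatment group presents them as how the technique works. The protocol names harms only for the exercise.
- *No symptom form exists for 40 weeks after week 12.* The role lists suggest so, but Statistical analysis plans a 6-month VISA-A. The document is inconsistent, so the gap is not established.
- *The therapist hears only of unexpected events.* That role is also the contact for any adverse event. What is missing is a duty to record or forward the expected ones.

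It may also be said that every arm is reviewed fortnightly with pain scored, that Limitations already discloses the difference in visit numbers, and that a SAP could hold the by-arm table. The reviews are not said to feed any harm record. The disclosure concerns the effect of treatment, not the ascertainment of events. A SAP can tabulate only what the protocol has had collected. The cited university policy and the study flow chart are not available, and either might add something.

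**Conclusion.** The point holds in limited form. The protocol provides only for reporting of unexpected events, through an unblinded therapist who gives the needling, and sets out no systematic collection of expected or minor adverse events by arm. VISA-A and the global rating cover net worsening in part and nothing else.

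Events that surface would come from 1.5 times as many contacts in the needled arms as in exercise alone if reviews share needling visits, or up to 2.5 times if they do not. The IMS-sham contrast is free of that imbalance but not of the unblinded reporter.

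This does not threaten the primary analysis. It does mean that a VISA-A benefit could be reported with little interpretable harm data beside it, and it should be corrected. The conclusion assumes that the unseen policy and flow chart add no event form.

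**What to change.** 1. **Study Team and Roles, treating therapist.** Have the therapist record all adverse events, expected or not. Keep prompt reporting of unexpected events as it is.
2. **One fixed self-completed item for all three arms** at 6, 12 and 52 weeks: new or worse pain, swelling, bruising or other problem since the last form, with severity and duration. Put it on a separate sheet. Participants complete it after the range-of-motion assessment and return it sealed to the front desk for the research assistant. The blinded assessor directs the other questionnaires and should neither see nor discuss this one, because a question about bruising invites disclosure of needling.
3. **Six months.** Reconcile the 6-month VISA-A analysis with the role lists, which provide no such form. If a 6-month form is used, the research assistant should send and collect it. The therapist acquires the ultrasound images and should not handle it.
4. **Outcome measures and Statistical analysis.** Add adverse events by arm, from this equal-schedule item, as a descriptive secondary outcome. State that zero events in 14 patients leaves a one-sided 95% upper limit of about 19%.

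The cost is one sheet at existing time points, some data entry, one table and more minor events to list. No new visit or staff is needed, and treatment does not change.
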